**Figure 1 figure1:**
[figure not shown]
Study Flow Chart.

### Control Condition

In the pacing only condition, participants will be educated about pacing to manage their daily energy levels and informed not to commence a physical activity program for 6 months. Pacing is a process whereby activities of daily living are organized and timed in order to not exceed the available energy for that particular day. Pacing will be self-monitored to avoid excessive exertion by means of continuous HR monitoring and RPEs maintained below a designated threshold. The HR and RPE thresholds will be determined during the baseline effort test, which is described in detail in the Methods section. Participants in the pacing only control condition will be provided with no instruction to increase physical activity levels.

### Intervention Conditions

The intervention will be 6 months in duration. In the pacing plus conventional activity condition, participants will be educated about pacing and prescribed a home-based participant-controlled symptom-contingent physical activity program involving a conventional activity type selected by the participant such as walking, elastic band resistance exercise, or cycling.

In the pacing and active video gaming condition, participants will be provided with an Xbox Kinect (set up in their home) and prescribed a home-based participant-controlled symptom-contingent physical activity program involving dance and sport games (Sports Rivals and Dance Central). Swapping passive screen time (such as television viewing) with the active gaming will be recommended. If the participants report no or minimal screen time, they will be encouraged to swap out other activities that require low cognitive or physical load. The active video gaming and conventional physical activity is intended to be additional to existing physical activities.

Participants in the two conditions involving physical activity (ie, pacing and conventional physical activity and pacing and active video gaming) will have their starting physical activity prescription developed by the research assistant who will be an accredited exercise physiologist with at least 2 years of clinical experience. The research assistant will develop the prescription based on participant self-reported amount of activity and symptom relationship from the Symptom History Questionnaire (detailed later in Methods section). Prescription will involve allocation to 1 of 3 tiers: light tolerance, moderate tolerance, or high activity tolerance (Table 1).

**Table 1 table1:** Physical activity prescription triage categories.

Activity tolerance tier	Categorization	Baseline	Progress
Exclude	Self-reported flare-up of symptoms with less than 5 minutes of screen time; moderate to severe symptom flare-up with less than 5 minutes of self-reported light physical activity or household chores	—	—
Light	Flare-ups with predominantly moderate to high intensity tasks or longer bouts of light intensity tasks or pushing energy envelope with too many activities on a given day; able to participate in light activity for at least 5 minutes (but less than 10 minutes)	2 minutes per day (6-8 minutes per week)	30 seconds to 1 minute per day per intervention week
Moderate	Symptom flare-ups with activities predominantly considered moderate or high intensity (ie, minimal flare-ups with light intensity tasks), able to be active for between 10 to 15 minutes at a light intensity with minimal or no flare-up of symptoms	5 minutes per day (15-20 minutes per week)	1 to 2 minutes per day per intervention week
High	Reported symptom flare-ups with activities predominantly considered high intensity or longer bouts moderate tasks (ie, minimal flare-ups with light intensity and short bouts of moderate intensity tasks), able to be active for 15 or more minutes at a light intensity with minimal or no flare-up of symptoms	10 minutes per day (30-40 minutes per week)	2 to 4 minutes per day per intervention week

Physical activity will be prescribed every second day (at the most) and perceived exertion will be monitored by the participant remaining under the set HR and RPE thresholds at all times. Participants will be in full control of their program and will be able to stop physical activity sessions entirely; plateau; or reduce frequency, duration, or intensity of sessions to manage symptom occurrences. Activity sessions can be completed in one session (eg, 1 10-minute block) or split up throughout the day.

Any activity progression will occur every 2 weeks. To be eligible to progress, participants must demonstrate symptoms are stable. Stable equates to HR and RPE zones adhered to for the 2-week period and no increase in symptoms as a result of activity. Progression can be escalated (particularly as higher volumes demonstrated) with consultation with research team and research assistant only if symptoms are stable. The active gaming or conventional activity will be encouraged on those days that the participants consider there to be adequate energy to do all activities of daily living usual for that person. Participants will also be encouraged to consider cognitive activities as potentially draining in addition to physical activities.

### Setting

Participants will be recruited from Adelaide, South Australia, Australia. Testing will occur during face-to-face sessions at the University of South Australia, City East Campus, Adelaide, Australia. Home visits will be conducted to educate the participants regarding their condition allocation and set up video games where applicable, and the remainder of the intervention will be home-based.

### Participants

Inclusion criteria:

Aged from 18 to 65 yearsGeneral practitioner clearanceSelf-reported diagnosis of ME/CFS by a general practitioner or medical specialist based on one of the commonly accepted criteria (the Oxford Criteria is not acceptable)Able to complete exercise test (either maximal or submaximal)Not currently playing active video gamesScore low to moderate on Sports Medicine Australia Exercise Screening Tool [21]Self-report less than 150 minutes of moderate intensity activity each week (not meeting Australian National Physical Activity Guidelines for adults [22])Have a television in their home (Internet not required) and be willing to develop video game literacy

Exclusion criteria:

Self-reported aggravation of symptoms with 5 or fewer minutes of screen timeSelf-reported aggravation of symptoms with 5 or fewer minutes of light intensity physical activity or movement

### Sample Size

This is the first study to investigate the feasibility and acceptability of active video gaming to increase the physical activity levels of people living with ME/CFS. A sample of 30 participants was deemed appropriate to provide the process feedback regarding testing procedures, and feasibility and acceptability data will be collected from 10 participants regarding the active video gaming experience.

### Recruitment

Participants will be recruited via local community support organizations, fliers, Facebook advertising, and the University of South Australia Clinical Trials Facility website.

### Feasibility and Acceptability

To explore the feasibility of implementation, total testing time will be calculated at each testing point for each participant. Statistics regarding the total amount and type of resources required (eg, consumables, printing) will be collected. Recruitment feasibility will be investigated after recruitment phase and involve analysis of recruitment statistics (eg, duration, ineligibility vs eligibility ratio number of recruitment avenues). Comprehensive informal exit interviews will be conducted with the active video game intervention group participants at the end of the intervention to explore acceptability either face-to-face or over the telephone. Information will be obtained on general satisfaction with the program, perceived cost effectiveness, acceptability of the testing protocols, and desire to continue with active video gaming.

### Effort Testing (Baseline Only)

Prior to randomization, participants will be screened for eligibility and will participate in either a maximal effort 2-day testing protocol or a submaximal effort protocol. A submaximal effort protocol has been included as an option as community feedback indicated unwillingness from some people due to the potential symptom flare-up predicted with the maximal protocol.

Effort testing on a bicycle ergometer is required to accurately determine the HR and RPEs at ventilatory threshold (VT) or 10% below the VT for each participant. This 10% below VT has been posited as a preferred limit to stay below to avoid symptom flare-up [23] and will be employed in this study for all 3 arms.

The 2-day maximal effort testing protocol is a smaller study running concurrently at the University of South Australia looking to confirm the differing physiological responses demonstrated by people with ME/CFS due to postexertional malaise during repeat exercise testing when compared to healthy controls. The 2-day maximal effort testing protocol will involve attending the university on 2 consecutive days and participating in the same testing protocol on a cycle ergometer wearing a gas analysis mask. A subjective questionnaire regarding fatigue status will be completed, followed by a 10-minute period of rest while wearing an HR monitor. The incremental exercise test on the bike will progress from very light to maximal exercise over a period of 8 to 12 minutes. The test starts with a 5-minute, 40 watt warm-up, during which rate of HR increase is assessed. Following this 5 minutes, the test increases using a ramp protocol, with increases of 5 watts every 20 seconds (so 15 watts per minute on average). The test finishes when the participant reaches volitional exhaustion. Both testing sessions will be conducted at the same time of day.

The submaximal effort testing alternative will involve attending the university on 1 occasion. Participants will complete 1 test on a cycle ergometer while wearing a gas analysis mask. Participants will exercise on a cycle ergometer commencing at a work rate of 25 watts and increasing by 15 watts each minute until a HR of 85% of age predicted maximum is achieved (208–[0.7×age]) [24]. The test will be terminated prior to this point if participant reaches voluntary exhaustion or reports an RPE of 19 or higher, respiratory exchange ratio of >1.15, or a plateau in HR or VO_2_ with increasing work rate. Recommended exercise intensity will be limited to an HR corresponding to 10% below measured VT or in the case that VT is not adequately detected in the exercise test then below 70% of age-predicted HR max.

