### Health-Related Outcomes

#### Overview

There will be at least 4 weeks between effort testing and commencement of the intervention with 2 weeks being stable at a pretest pattern of symptoms/activity. Participants may require longer recovery before commencing the intervention.

All health-related outcomes will be measured at 3 time points: baseline, 6 months after baseline at the end of the intervention, and at 6-month follow-up after the intervention has been completed. In addition, accelerometer, inclinometer, and continuous captured HR will be measured during week 6, week 12, and week 18 of the intervention. The Karnofsky Scale [25] will be collected more frequently, with the research assistant recording the Karnofsky Scale value each time telephone contact is made with a participant.

Health-related outcomes have been chosen after extensive consultation with the stakeholder advisory group which included people living with ME/CFS. Outcomes have been selected to first provide data on the primary health-related outcomes (ie, physical activity and allostatic load:11 variables). Outcomes have also been selected to cover client-centered outcomes such as use of time, quality of life, and functioning. These outcomes are of utmost importance to the people with ME/CFS and capture the broader International Classification of Functioning, Disability, and Health framework concepts of activity limitations and participation restriction [26]. Finally, outcomes have been selected to capture the vast range of symptoms reported by people with ME/CFS to ensure the levels are monitored alongside the physical activity changes to ensure safety and investigate net benefit to the participants.

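### When VT is not detected, the heart-rate ceiling depends on age alone, so it can sit close to or above the heart rate at which that participant stopped exhausted

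*Protocol article*

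**What the plan says.** All references are to the Methods of the protocol article.

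- **Main rule (Effort Testing).** "Recommended exercise intensity will be limited to an HR corresponding to 10% below measured VT". The purpose is given in the same section: "This 10% below VT has been posited as a preferred limit to stay below to avoid symptom flare-up". The limit applies in all 3 arms.
- **Fallback (same section).** "in the case that VT is not adequately detected in the exercise test then below 70% of age-predicted HR max". Age-predicted maximum is 208 − 0.7 × age.
- **How the tests end (same section).** The submaximal test aims for 85% of age-predicted maximum, but "The test will be terminated prior to this point if participant reaches voluntary exhaustion or reports an RPE of 19 or higher". A respiratory exchange ratio above 1.15 or a plateau in HR or VO2 also ends it. The 2-day maximal test ends at volitional exhaustion. No minimum HR is set for either test.
- **Use of the limits.** Control Condition: "The HR and RPE thresholds will be determined during the baseline effort test". Intervention Conditions, for the two activity arms: "perceived exertion will be monitored by the participant remaining under the set HR and RPE thresholds at all times".

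**The concern.** The main rule protects itself. VT is found within the participant's own test, so an HR corresponding to 10% below VT lies under the highest HR reached in that test. The fallback loses this property because age is its only input. A person who stops early and a person who reaches the planned end point get the same ceiling if they are the same age.

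For someone who was exhausted near or below 70% of predicted maximum, the HR limit then allows activity up to, or beyond, the HR at which the cycle test had to stop. For that person it does little to keep exertion below a flare-up level. It also makes the HR part of the progression rule easier to meet, since a stable period is defined partly by staying within the HR zone. The two conditions may go together, because a test cut short is a plausible case for VT not being detected.

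What is at stake is participant safety and dose setting.

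**Working it through.** **Inputs from the article:** predicted maximum = 208 − 0.7 × age; fallback = 70% of it; planned submaximal end point = 85% of it; age range 18 to 65. **Assumption:** the article reports no stopping HRs, so stops at 60%, 65% and 71% of predicted maximum are illustrative. The article states no bpm figures to reproduce.

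**Step 1. Fallback against an assumed stop below 70%.** Gap = 0.70 × maximum − stopping HR, in bpm.

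| Age | Maximum | Fallback (70%) | End point (85%) | Stop at 65% (gap) | Stop at 60% (gap) |
|---|---|---|---|---|---|
| 18 | 195.4 | 136.8 | 166.1 | 127.0 (+9.8) | 117.2 (+19.5) |
| 40 | 180.0 | 126.0 | 153.0 | 117.0 (+9.0) | 108.0 (+18.0) |
| 65 | 162.5 | 113.75 | 138.1 | 105.6 (+8.1) | 97.5 (+16.25) |

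As a ratio, the ceiling is 0.70/0.65 = 108% of the stopping HR for a stop at 65%, and 0.70/0.60 = 117% for a stop at 60%.

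**Step 2. Just above 70%.** At age 40 a stop at 71% is 0.71 × 180 = 127.8 bpm. The ceiling of 126 is 126/127.8 = 98.6% of that. So 70% is only where the two numbers cross; it is not a safety boundary. At the planned 85% end point the ceiling is 0.70/0.85 = 82% of the HR reached, so someone who completes the submaximal test as planned is not in this position.

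**Step 3. With a margin.** Take 10% below the stopping HR as an example, so that ceiling = min(0.70 × maximum, 0.90 × stopping HR). The second term binds when the stop is below 0.70/0.90 = 77.8% of predicted maximum, which is 140 bpm at age 40. At age 40:

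- stop at 127.8: ceiling 115.0 instead of 126, lower by 11.0;
- stop at 117: ceiling 105.3 instead of 126, lower by 20.7;
- stop at 108: ceiling 97.2 instead of 126, lower by 28.8.

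A cap at the stopping HR with no margin would give 117 and 108 in the last two cases, lower by 9 and 18. That still allows activity up to the exhaustion HR, so a margin is needed to serve the stated purpose.

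**Step 4. How many participants.** The article gives no rate of undetected VT or of early exhausted stops. Any expected count among the 30 would only restate an assumed rate, so none is given.

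**The case against.** The strongest case is that this is an edge case already covered by other means.

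- **Two events must coincide.** VT must be undetected, and the test must end in exhaustion at a low HR. This stands: the number affected is unknown and may be zero.
- **Eligibility may remove the case.** Participants must be able to complete one of the tests, and someone exhausted well before 85% may not count as having completed the submaximal one. This stands in part. Completion is not defined, early termination is a listed way for that test to end, and the maximal test is complete at exhaustion whatever the HR.
- **The fallback is an upper bound.** The exercise physiologist may set a lower figure. True, but nothing requires it.
- **RPE also binds.** Whichever limit is reached first applies. This is real protection, but Effort Testing ties the RPE limit to VT as well, and the fallback it states is for HR only.
- **Exposure is small and watched.** Sessions start at 2, 5 or 10 minutes, every second day at most. Participants may stop at will, progression needs no increase in symptoms, calls are regular with adverse-event and Karnofsky questions, and "continuous captured HR will be measured during week 6, week 12, and week 18 of the intervention". All of this stands and limits the harm.
- **A cycling stop HR need not be the highest HR possible in other tasks.** This also stands. It is a reason to let the medical advisers choose the margin.
- **The procedures were reviewed.** The third consultation round clarified the effort tests, and the stakeholder group endorsed the protocol. That shows care, but the rule as printed still has no link to the HR reached.

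A reader might go further and infer that affected participants are left unprotected, that many are affected, or that the trial's results would be distorted. The documents support none of these. The safeguards above operate independently of the HR figure, no frequency is given, and nothing ties the ceiling to a bias in the estimates.

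**Conclusion.** The point holds as a minor safety improvement. The fallback can place the HR ceiling close to or above the HR at which a participant stopped exhausted or at RPE 19 or more, contrary to the purpose stated for the limit. For assumed stops at 65% to 60% of predicted maximum the excess is about 8 to 20 bpm across ages 18 to 65. For a stop just above 70% the ceiling is almost equal to the exhaustion HR.

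That the ceiling can exceed the stopping HR follows from the article's rules alone. The sizes rest on assumed stopping HRs. The conclusion also reads the fallback as covering both tests: the sentence sits in the submaximal paragraph but refers to the exercise test in general. Few or none of the 30 participants may be affected.

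**What to change.** Add one rule to Effort Testing. Where VT is not adequately detected and the test ended for exhaustion or RPE of 19 or more, set the HR ceiling below the lower of (a) 70% of age-predicted maximum and (b) the observed stopping HR less a stated margin. The medical advisers should set that margin. A margin of 10% would mirror the figure in the main rule, although there it refers to VT and not to stopping HR. For the 2-day maximal test, use the lower of the two days' stopping HRs. Record for each participant whether VT, the age-based fallback or the stopping HR set the ceiling.

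The cost is one sentence and one record field. No new test is needed, because HR is already followed during the effort test. The downside is a tighter HR limit for those affected, including during daily activities. With a 10% margin it is about 11 to 29 bpm lower at age 40 for assumed stops from 71% down to 60%. The advisers should weigh that restriction when choosing the margin.

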### Health-Related Outcomes

#### Overview

There will be at least 4 weeks between effort testing and commencement of the intervention with 2 weeks being stable at a pretest pattern of symptoms/activity. Participants may require longer recovery before commencing the intervention.

All health-related outcomes will be measured at 3 time points: baseline, 6 months after baseline at the end of the intervention, and at 6-month follow-up after the intervention has been completed. In addition, accelerometer, inclinometer, and continuous captured HR will be measured during week 6, week 12, and week 18 of the intervention. The Karnofsky Scale [25] will be collected more frequently, with the research assistant recording the Karnofsky Scale value each time telephone contact is made with a participant.

Health-related outcomes have been chosen after extensive consultation with the stakeholder advisory group which included people living with ME/CFS. Outcomes have been selected to first provide data on the primary health-related outcomes (ie, physical activity and allostatic load:11 variables). Outcomes have also been selected to cover client-centered outcomes such as use of time, quality of life, and functioning. These outcomes are of utmost importance to the people with ME/CFS and capture the broader International Classification of Functioning, Disability, and Health framework concepts of activity limitations and participation restriction [26]. Finally, outcomes have been selected to capture the vast range of symptoms reported by people with ME/CFS to ensure the levels are monitored alongside the physical activity changes to ensure safety and investigate net benefit to the participants.

#### Adherence Diary

All 3 groups will be provided with a pen and paper adherence diary to complete daily for the 6-month duration of the intervention. The pacing only group will document adherence to pacing protocol and HR achieved (yes/no) and RPE limit achieved (yes/no). The conventional physical activity and video games groups will document minutes of activity, specific day, HR achieved (yes/no), and RPE limit achieved (yes/no).

#### Sociodemographic Questionnaire

A sociodemographic questionnaire developed for the purpose of this study will capture data such as age, gender, education level, working/volunteer status, income, and duration of conditions.

#### Symptom History Questionnaire

A questionnaire developed for this study will capture all symptoms related to ME/CFS and also the relationship between symptoms and activity to assist in the pacing and activity protocol prescription for each individual.

#### Accelerometer

GENEActiv (Active Insights Ltd) accelerometers will be worn on the nondominant hand for 7 days during each testing period. Accelerometers will be worn for 24 hours per day but will be removed for bathing and swimming activities. Participants will complete a log to report periods of nonwear time and sleep/nap times.

#### Inclinometer

ActivPAL (PAL Technologies Ltd) inclinometers are matchbox-sized devices that measure position relative to gravity. They are worn on the front of the thigh attached with hypoallergenic adhesive tape for a period of 7 days and report the minutes spent sitting, standing, and walking. Inclinometers are the current gold standard measurement of sitting/reclining time, a measure of sedentary time.

